## **14. Statistical considerations**

### **14.1 Sample size**

The unit of randomisation is city/town (the clusters), each cluster will recruit 25 participants (based on maximum possible caseload for each Peer Navigator) in the intervention arm and 30 participants in the control arm. A trial of 20 clusters will recruit 550 participants: we anticipate an attrition rate of up to 40% in the intervention arm and 50% in the control arm, based on feasibility work/related research resulting in outcome data on 300 participants (150 in each arm), equating to mean cluster size of 15. Assuming an ICC of 0.01 this design has 90% power to detect a 0.4SDs effect size. We will work our PPI collaborators to maximise retention in the study, refining processes as we go.

As part of the process evaluation, interviews will be undertaken with staff in the intervention services and with all the 10 Peer Navigators, to understand experiences of, and views on, the intervention from a range of perspectives, and to collect data on changes in the trial contexts during the study:

- Staff in a range of roles in intervention clusters (n=10)
- External stakeholders, including commissioning roles in intervention clusters (n=10)
- Staff in a range of roles in control clusters (n=10)
- Peer Navigators (n=20, i.e., all 10 Peer Navigators at two time points, pre and post intervention)

We will conduct the NoMad questionnaire [40] with a sample of staff (n=4-5) in each intervention setting at three time points (start, middle and end of intervention, aiming for a total sample size of 100-120).

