### 14.7 Success and progression criteria

We have set two targets: one to assess the opening of the clusters as recruitment sites, and the other the recruitment of participants. We propose one decision point at month 10 of the study, to be assessed by the Trial Steering Committee, and our progression criteria are laid out in Table 3 below. We have built contingency into the timetable to take account of unpredictable service demands. There is no internal pilot phase given the short period of recruitment of both clusters and participants.

**Table 2:** Stop/go criteria at 10 months

|                 | GREEN              | AMBER                   | RED                  |
|-----------------|--------------------|-------------------------|----------------------|
| Cluster opening | 100% (20 clusters) | 70-95% (14–19 clusters) | < 70% (<14 clusters) |

|                                 |                               |                                   |                                |
|---------------------------------|-------------------------------|-----------------------------------|--------------------------------|
| Participant recruitment* | 100% (12.5 per cluster month) | 60-96% (7.5–12 per cluster month) | < 60% (<7.5 per cluster month) |
|---------------------------------|-------------------------------|-----------------------------------|--------------------------------|

\* For participants, stop/go will be based on expected number of participants recruited given the number of clusters open to recruitment, to distinguish between cluster- or participant-level barriers to recruitment.

Figure 3 shows the recruitment of clusters and participants over the four-month recruitment phase. Our projection is based upon 20 clusters contributing 25 or 30 participants each over two months. Incorporating a staggered cluster set-up, we would expect to recruit 65 participants in month 7, 500 by the end of month 9, and the remaining 50 in month 10. Recruitment is based upon throughput from our previous feasibility study, use of study-specific researchers to recruit, and having existing ‘pools’ of participants in the cluster services.

**Figure 3:** Recruitment projection

[figure not shown]

To determine success criteria and barriers, we have a risk/mitigation plan with a selection of issues below.

**Table 3:** Risks and mitigations

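### The GREEN recruitment rate of 12.5 per cluster-month delivers 500 participants, not the 550 that the trial plans

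*Protocol*

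**What the plan says.** Section 14.7 (Success and progression criteria) sets one decision point, at month 10, and states that there is no internal pilot. The participant row of Table 2 reads:

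- GREEN: "100% (12.5 per cluster month")
- AMBER: "60-96% (7.5–12 per cluster month")
- RED: "< 60% (<7.5 per cluster month")

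A footnote to that row says that "stop/go will be based on expected number of participants recruited given the number of clusters open to recruitment". Below the table, the same section states: "Our projection is based upon 20 clusters contributing 25 or 30 participants each over two months". It then projects "500 by the end of month 9, and the remaining 50 in month 10", which makes 550.

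Section 14.1 (Sample size) agrees: "A trial of 20 clusters will recruit 550 participants". It also says that "each cluster will recruit 25 participants (based on maximum possible caseload for each Peer Navigator) in the intervention arm", and it sets 30 for each control cluster.

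**The concern.** A threshold labelled 100% should correspond to the planned sample. The three rates in Table 2 fit 25 participants in every cluster, but the plan is 25 in intervention clusters and 30 in control clusters.

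This is the only progression decision in the trial. The control clusters were given the larger number because 50% attrition is expected there, against 40% in the intervention arm. A committee reading Table 2 literally could record full recruitment while the control arm lacked exactly the participants added to offset that attrition. At the lower end, it could record AMBER at a rate that is below 60% of the real target.

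**Working it through.** **Inputs.** Twenty clusters; 25 per intervention cluster and 30 per control cluster; 550 in total; attrition up to 40% and 50%; ICC 0.01; effect 0.4 SD; 90% power (section 14.1). Ten Peer Navigators in ten towns or cities (Trial summary), one per intervention cluster (section 7.1), leave ten control clusters. Two months of recruitment per cluster (section 14.7). Section 14.1 gives no significance level, so two-sided 5% is assumed, in line with the 95% confidence intervals in section 14.4.

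**1. The plan's own figures reproduce.**
- Recruits: 10 × 25 + 10 × 30 = 550.
- Completers: 250 × 0.6 = 150 and 300 × 0.5 = 150.
- Design effect at 15 per cluster: 1 + 14 × 0.01 = 1.14.
- Standard error in SD units: √(1.14/150 + 1.14/150) = √0.0152 = 0.1233.
- Power: Φ(0.4/0.1233 − 1.96) = 90.1%.

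**2. The base of the Table 2 percentages.** 7.5/12.5 = 60% and 12/12.5 = 96%. All three bands therefore use 12.5 as their base, which is 25 participants over two months.

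**3. What that base delivers.** 12.5 × 2 × 20 = 500, and 500/550 = 90.9%.

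**4. The rate that the plan needs.** 20 × 2 = 40 cluster-months, and 550/40 = 13.75. By arm, 25/2 = 12.5 and 30/2 = 15. The printed rate is right for intervention clusters and is 12.5/15 = 83.3% of the control rate.

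**5. The band edges against 550.**

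| Edge in Table 2 | Recruits over 40 cluster-months | Stated % | % of 550 |
|---|---|---|---|
| 12.5 (GREEN) | 500 | 100 | 90.9 |
| 12 (top of AMBER) | 480 | 96 | 87.3 |
| 7.5 (AMBER/RED) | 300 | 60 | 54.5 |

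Sixty per cent of 13.75 is 8.25 per cluster-month, or 330 participants. Totals from 300 to 329 would read AMBER although they are below 60% of 550.

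**6. The gap.** AMBER stops at 12 and GREEN starts at 12.5. On the table's own base, totals of 481 to 499 have no band.

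**7. Effect on power if every cluster recruits exactly at GREEN.**
- Recruits are 250 per arm. Completers are 250 × 0.6 = 150 and 250 × 0.5 = 125, in control clusters averaging 12.5.
- The control design effect is 1 + 11.5 × 0.01 = 1.115.
- Standard error: √(1.14/150 + 1.115/125) = √(0.00760 + 0.00892) = 0.1285.
- Power: Φ(0.4/0.1285 − 1.96) = 87.5%.
- With a t reference on 20 − 2 = 18 degrees of freedom, the two figures are 86.6% (150 v 150) and 83.7% (150 v 125).

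**The case against.** The strongest reply is the footnote. It bases the decision on an expected number given the clusters open, and the projection in the same section builds its expected number from 25 or 30 per cluster. On that reading the committee would judge against 550, and 12.5 would only be a mislabelled rate. However, the footnote adjusts for how many clusters are open. It gives no rate for control clusters and leaves 12.5 printed as 100%. Either the printed rates are used and the target is wrong, or a 25/30 expectation is used and the printed rates are wrong.

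Several other points limit the size of the finding:

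- The shortfall of about 9% is a pooled average. Intervention clusters have the right rate, and control clusters have one about 17% too low.
- The figure of 500 depends on two months per cluster. At 12.5 per cluster-month, 550 would take 550/12.5 = 44 cluster-months, or 2.2 months per cluster. That is possible in practice, but it is not the stated projection.
- The attrition figures are upper limits, so 150 and 125 completers are worst-case counts. The control arm would still start with 250 instead of 300.
- For a single cluster over two months, 12 and 12.5 mean 24 and 25 participants, with no whole count between. The gap matters only for averages across clusters, which is how a trial-level criterion is likely to be read.
- GREEN does not change the sample size. Section 7.1 still aims for at least 30 per control cluster, and a committee would probably also see the actual counts against 550.

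The control ranges do not rescue the rate. Section 5 allows 25 to 35 per control cluster and section 7.1 allows up to 35 to offset smaller clusters, but the planned total remains 550.

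**Conclusion.** The point holds. Table 2 conflicts with the projection in its own section and with section 14.1. Its 100% rate yields 500 participants, which is 50 short of 550, and the whole deficit is in the control arm when each cluster just meets the rate. The 60% line lies at 54.5% of target.

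The cost in power is modest, about 2.5 percentage points on the normal approximation and 2.9 on 18 degrees of freedom. It does take the trial below its stated 90% while the criterion reads as fully met. These figures assume two months per cluster, ten clusters per arm, attrition at the stated limits, ICC 0.01 and a two-sided 5% test.

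The amendment history records a version 3 change to the control-cluster sample size. That suggests a rate carried over from 25 per cluster, but this is an inference and the finding does not rest on it. The row should be corrected because it governs the only progression decision.

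**What to change.** Replace the participant row of Table 2 with rates based on 13.75 per cluster-month: GREEN at 13.75 or more, AMBER from 8.25 to below 13.75, RED below 8.25. These bands are contiguous and keep the existing 60% line.

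Alternatively, judge each arm against its own rate, 12.5 for intervention and 15 for control. This would show a control-arm shortfall directly. In either case, the footnote should say that the expected number is built from 25 per open intervention cluster and 30 per open control cluster.

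If the month-10 decision has already been taken, re-express it against 550 in the trial report, by arm.

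The cost is one table row and one sentence in the footnote. The only drawback is that GREEN becomes slightly harder to reach.

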## 15. Health economic evaluation

A full economic evaluation will be conducted from a public sector perspective. This will take the form of a cost-utility analysis. We will also conduct a cost-consequence analysis which will identify, and where possible measure, all costs, and consequences (effects) of the intervention, compared to control. Given that the intended effects of the intervention are wider than health effects, we will estimate both an incremental cost per quality-adjusted life year (QALY) gained and an incremental cost per Years of Full Capability (YFC) gained. Capability is measured using the ICECAP-A measure which measures broader wellbeing.

The direct intervention costs include the salary costs of the Peer Navigators, and costs borne by The Salvation Army. Public sector perspective costs will include costs of health and social care (primary care, secondary care, community care, medication), criminal justice services, and housing services. Resource use estimates will be combined with unit costs obtained from standard sources or study specific estimates. Total costs will be reported, as well as total costs by organisation. Incremental costs for the SHARPS intervention versus control will be estimated using mixed effects generalised linear models, with appropriate distributions for cost data and adjustment for baseline covariates.

We will measure benefits in terms of QALYs gained, based on participant responses to the generic EQ-5D-5L health-related quality of life measure [46], and in terms of YFC, based on participant responses to the ICECAP-A capability measure [47]. Both are measured at baseline, 6, 12 and 15

months. The EQ-5D-5L and ICECAP-A responses will be converted into utility scores using published population tariffs. Incremental QALYs and YFCs for the SHARPS intervention versus control will be estimated using mixed effects generalised linear models, with adjustment for baseline covariates.

Costs and benefits will be combined to estimate incremental cost per QALY gained and incremental cost per YFC gained for the SHARPS intervention versus control over the trial follow up period. Deterministic sensitivity analyses will be undertaken to test the impact of assumptions and analysis methods on results. A comprehensive set of sensitivity analyses, including exploration of appropriate missing data models will be undertaken to explore uncertainty in our conclusions. Results will be plotted on the cost-effectiveness planes to illustrate the impact of sampling uncertainty on results. The cost consequence analysis will be presented as a balance sheet listing all relevant costs and effects.

## **16. Process evaluation**

In terms of methodological theory, within our SHARPS feasibility study, NPT guided the development/implementation of the intervention, as well as the process evaluation. NPT comprises four components: coherence (understanding), cognitive participation (buy-in), collective action (making it work), and reflexive monitoring (on-going appraisal). For the SHARPS cRCT we will draw on May et al.'s [48] coding manual to facilitate transparent data analysis processes and reduce the cognitive and practical burden on researchers. This manual also links the 12 primary NPT constructs to realist evaluation methods by conforming to the Contexts-Mechanisms-Outcomes configuration that realist approaches centre upon. We will conceptually draw upon realist frameworks. To interpret findings, we will also use a range of theories/frameworks, such as the modified access model by Penchansky and Thomas [49], and on peer support, such as Barker et al.'s (2020) model of change mechanisms within unidirectional peer support [50]. We will examine the impact on the Peer Navigators using literature on task shifting, organisational cultures, social bonds, and intersectionality.

The analysis will identify contextual influences on implementation across settings: how individuals understood, adopted, or perceived the intervention; how participants engaged with/disengaged from the intervention; how staff experienced hosting the intervention and being in the control (standard care) settings; how the Peer Navigators made sense of role; and other contextual factors impacting delivery. Analysis will be undertaken using the Framework approach and NVivo software will be used to organise and code data to support the process of analysis. All stages of Framework will be closely followed. To enhance rigor and validity, the trial EbyE group will participate in data analysis/interpretation to act as a form of 'member checking' to enhance the validity and trustworthiness of the findings. As part of the process evaluation, we will also take a mixed methods approach to assess intervention fidelity, this will include the use of an adapted existing fidelity index.

## **17. Experts by Experience group**

Our EbyE group will be closely involved in the research process throughout the trial. This includes co-producing all participant materials to ensure they are easy to understand, participating in data analysis and interpretation to act as a form of 'member checking' to enhance the validity and trustworthiness of the findings, and collaborating to produce study outputs. The EbyE group will meet every six months throughout the trial chaired by [name] and [name] and will comprise of individuals with lived/living experience of homelessness and/or substance use (and related challenges), including some of those involved in the SHARPS feasibility study.

## **18. Data monitoring**

### **18.1 Source data**

The study is set-up such that quantitative data can be captured electronically directly into the study database. We anticipate that the majority of quantitative data will be captured in this way, and therefore the source document is the electronic record. Researchers will have access to paper copies of data collection tools as a failsafe if, for example, there is no wi-fi or 4G internet access. If paper copies of data collection tools are used, these will be considered to be the source document and retained in the study record. Any paper copies will be returned to the University of Stirling, scanned and uploaded to the SharePoint site.

### **18.2 Data monitoring**

Data collected by Researchers will be reviewed by the trial office staff to identify data queries and/or missing data. Data queries will be raised to try and ensure a complete and accurate data set. Extensive range and consistency checks will further enhance the quality of the data. Cleaning will take place ahead of each Data Monitoring and Ethics Committee meeting.

### **18.3 Clinical governance issues**

To ensure responsibility and accountability for the overall quality of care received by participants during the trial period, clinical governance issues pertaining to all aspects of routine management will be brought to the attention of the Trial Steering Committee and, where applicable, to local The Salvation Army services.

## **19. Quality assurance and ethical considerations**

### **19.1 Quality assurance**

The trial will be conducted in accordance with the MRC Good Clinical Practice guidance and the Research Governance Framework for Health and Social Care. Universities (Aberdeen/Stirling) have codes of practice for secure data management, researcher conduct and safety.

### **19.2 Ethical considerations**

The main ethical considerations are ensuring use of appropriate lay language, confidentiality/anonymity, data protection, participant burden, disclosure of risk, safety of researchers, safety of Peer Navigators, and dealing with the end of the intervention in a sensitive manner. Our EbyE group will ensure that all study materials are written using lay language. All research staff and Peer Navigators will sign a form stating confidentiality/anonymity will be adhered to. Participants may feel the burden of completing the measures at several time points (as well as the potential to also be interviewed), particularly those in the standard care sites. We will provide refreshments and vouchers to those completing the outcome measures and vouchers and refreshments to interview participants; study requirements will be clearly explained to all potential participants. We will comply with HRA Guidance for Informed Consent and GDPR. Participants will be asked to state clearly that they accept and understand limitations to confidentiality within the qualitative interviews. These limitations refer to disclosures of current or future intent to harm themselves or others.

If such disclosures do occur, these will be shared with service staff who will conduct a risk assessment as per their duty of care. The individual who has taken the disclosure would discuss course of action with study leads and an adverse events form completed. Staff safety will be ensured, with researchers following clear safety protocols, and risk assessments will be conducted,

and Peer Navigators provided with support/training around safety. Finally, we will use the learning from the SHARPS feasibility study regarding ending the intervention to ensure that transition support is in place. Ethical approval for this trial has been granted by University of Stirling (Ref: NICR 2024 16751) and The Ethics Subgroup of the Research Coordinating Council of The Salvation Army.

### **19.3 Study amendments**

Substantial amendments to the study (such as reduction of outcome measures) should be discussed by the Project Management Group, and where appropriate the Trial Steering Committee and Data Monitoring and Ethics Committee. Amendments to the protocol are reviewed by the funder after ethics approvals are sought.

### **19.4 Urgent safety measures and serious breaches of good clinical practice**

The study lead and research staff may take immediate safety measures to protect research participants against any hazard to their health or safety without prior authorisation from the research ethics committees or sponsor. However, they must alert the sponsor as soon as possible.

In the event that a serious breach of good clinical practice (GCP) is suspected, this will be reported to the sponsor and two ethics committees immediately and will be investigated by the sponsor. Any corrective action required will be undertaken by the study lead and ethics committees will be informed. If necessary, a protocol amendment will be submitted for review.

### **19.5 Satellite studies**

It is recognised, that the value of the trial may be enhanced by smaller ancillary studies of specific aspects. Plans for these will be discussed in advanced with the project management group and, if appropriate, with the Trial Steering Committee. Depending on the nature of the satellite trial, the Sponsor may consider this to be an amendment to the ethical approval for the study, or to require ethical approval as a project in its own right.

## **20. Confidentiality**

All information shared within a data collection context will be kept confidential unless there are reasons to breach confidentiality. In addition, participants will be asked to clearly state that they accept and understand limitations to confidentiality within interviews/data collection sessions. These limitations refer to disclosures of current, potential, or future intent to harm themselves or others, or harm to themselves from other parties. The disclosure from the participant must include clear indication/intent of current (active) or future threats of significant harm towards a specified person or themselves. Significant harm includes but is not limited to self-harm, suicidal thoughts, the use of weapons, sexual or physical violence, and general safeguarding concerns for children and vulnerable adults. If such disclosures do occur, this information will be shared with Study Leads, Service Managers and/or The Salvation Army study senior leads as appropriate who will take actions as needed according to organisational policies and procedures.

All data will be anonymised or pseudonymised, and all information that may be used to identify participants will be altered or removed. Each participant will be allocated a unique identifier study code which will be detailed on their consent form. Data will be collected, stored, and accessed in accordance with GDPR. The study team has a data protection/confidentiality agreement with the external transcriber. The audio files will be deleted once they have been transcribed/checked. To protect the identity of study participants, no names will be used in the reporting of the study. We will instead use numerical IDs followed by generic role descriptors such as 'staff' and 'external stakeholder'.

